### Randomization and Allocation

Baseline evaluation will be conducted for eligible subjects. All eligible patients will be stratified according to early, moderate, and advanced stages of glaucoma [14]. Patients with early glaucoma exhibit early glaucomatous visual field impairment, as characterized by a mean deviation (MD) of >–6 dB. Conversely, patients with moderate glaucoma present a moderate glaucomatous visual field loss, defined as MD≤–6 to ≥–12 dB. Patients with advanced glaucoma experience advanced glaucomatous visual field loss, defined as MD<–12 dB. SAS software will be used to automatically generate a set of random numbers ranging from 001 to 192. These numbers will be further classified into 3 ranges based on the disease stage. The early stage will incorporate random numbers from 001 to 064, the moderate stage will encompass numbers from 065 to 128, and the advanced stage will comprise numbers from 129 to 192. Following stratification, the participants will be assigned randomly to either an experimental group or a control group in a 1:1 ratio. Random numbers will be inserted into identical envelopes of equal dimensions, which will then be sealed to ensure concealment of group allocation and minimize the risk of selection bias. The random sequence allocation will be preserved and withheld from the investigators, statisticians, and outcome assessors to avoid detection bias.

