### Sample Size Calculation

The sample size calculation was based on previous studies. The basis of optic nerve protection effectiveness is 70% [16,17]. We hypothesized an 80% effective rate of the basis of optic nerve protection + press needles for GPCI in a larger sample size. According to the sample size of the estimation formula [18], α=.05 and β=0.10 in a 2-sided test, *P*_1_=.67 and *P*_2_=.87, 2-sided u_α/2_=u_0.05/2_=1.96, and 1-tailed u_β_=u_0.1_=1.282. We substituted these values into the following formula:

This resulted in n^1^=n^2^=79.02, that is, approximately 80 cases each in the experimental and the control group, or 160 cases in both groups. To account for a 20% dropout rate, the calculation 160 + (160 × 20%) = 192 suggested that 192 patients be recruited.

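### The sample size paragraph gives two different pairs of rates, the stated 79.02 per arm reproduces from neither, and 80 evaluable per arm falls short of 90% power under both

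*Protocol article*

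**What the plan says.** All of the calculation stands in one paragraph of the Protocol article, under Sample Size Calculation.

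- Rates in the prose: the control rate on basic optic nerve protection is given as 70%. For the experimental arm, "We hypothesized an 80% effective rate of the basis of optic nerve protection + press needles for GPCI". That is a gain of 10 percentage points.
- Rates and error levels entered: "α=.05 and β=0.10 in a 2-sided test, *P*_1_=.67 and *P*_2_=.87". That is a gain of 20 points. The change from 70/80 to 67/87 is not explained.
- Normal deviates: "2-sided u_α/2_=u_0.05/2_=1.96" and "1-tailed u_β_=u_0.1_=1.282".
- Result: "This resulted in n^1^=n^2^=79.02, that is, approximately 80 cases each in the experimental and the control group", so 160 in total, raised by 20% for dropout to 192.

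Randomization and Allocation confirms equal arms: patients are "assigned randomly to either an experimental group or a control group in a 1:1 ratio". The Abstract and the Results section report 220 recruited by October 2024, of whom 192 are expected to complete.

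**The concern.** The paragraph sets out a full calculation, so it can be checked, and it fails in two ways. It names two effect assumptions that cannot both hold, and its answer follows from neither.

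This paragraph is the article's only justification of the trial's size and the only source of its power claim (β = 0.10). A reader who relies on 90% power needs to know for which difference, and with how many evaluable patients, that figure applies. As written, the reader cannot tell whether the trial was sized for a 10-point or a 20-point gain, and the required n differs more than fourfold between them (392 against 91 per arm).

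**Working it through.** **Inputs.** All from Sample Size Calculation: two-sided α = 0.05 with u_α = 1.96; β = 0.10 with u_β = 1.282; rates .67/.87 (entered) and .70/.80 (prose). Allocation is 1:1. Hence (1.96 + 1.282)² = 10.5106.

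The printed equation is missing from the text available for this review, so the usual forms were all tried. Write d = P2 − P1, p̄ = (P1 + P2)/2, V0 = 2p̄(1 − p̄), V1 = P1(1 − P1) + P2(1 − P2), and h = 2·arcsin√P2 − 2·arcsin√P1.

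- A, pooled null and unpooled alternative: n = (u_α√V0 + u_β√V1)² / d²
- B, unpooled: n = (u_α + u_β)² V1 / d²
- C, pooled throughout: n = (u_α + u_β)² V0 / d²
- D, arcsine: n = 2(u_α + u_β)² / h²

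**Attempt to reproduce 79.02 from the entered rates.** For .67/.87: p̄ = .77, V0 = .3542, V1 = .3342, d² = .04, h = .48615.

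- A: (1.96 × .59515 + 1.282 × .57810)² / .04 = 90.97
- B: 10.5106 × .3342 / .04 = 87.82
- C: 10.5106 × .3542 / .04 = 93.07
- D: 2 × 10.5106 / .23635 = 88.94

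The nearest, 87.82, is 11% above 79.02 (87.82/79.02 = 1.11). Continuity correction moves further away: 100.73 for A and 97.56 for B.

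**From the rates in the prose.** For .70/.80: p̄ = .75, V0 = .375, V1 = .370, d² = .01, h = .23198.

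| Formula | .67/.87 | .70/.80 |
|---|---|---|
| A | 90.97 | 392.06 |
| B | 87.82 | 388.89 |
| C | 93.07 | 394.15 |
| D | 88.94 | 390.61 |

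The .70/.80 figures are about five times the stated n (388.89/79.02 = 4.9).

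**Could a different α or β explain it?** For .67/.87, values near 79 appear only when a stated input is changed: 77.92 (A) or 79.48 (C) at 85% power, 78.01 (A with continuity correction) at 80% power, 81.27 (B with continuity correction) at one-sided α. None equals 79.02, and the printed 1.96 and 1.282 rule them out.

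**Where 79.02 may come from.** A search of whole-percent pairs from 50% to 99% under A to D returns 79.02 once: D with 70% vs 90%. There h = .51578, and 2 × 10.5106 / .26603 = 79.02. The article never states that pair, so this is an inference about the origin of the number.

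**Power.** Formula A solved for power: Φ[(d√n − 1.96√V0) / √V1]. For .67/.87 at n = 80: (.20 × 8.9443 − 1.96 × .59515) / .57810 = 1.077, and Φ(1.077) = .859. For .70/.80 at n = 80: (.10 × 8.9443 − 1.96 × .61237) / .60828 = −.503, and Φ(−.503) = .308.

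| Evaluable per arm | Basis | .67/.87 | .70/.80 |
|---|---|---|---|
| 80 | the protocol's own target | 85.9% | 30.8% |
| 77 | 192 less 20% (192 × 0.8 / 2 = 76.8) | 84.6% | 29.8% |
| 96 | all 192 evaluable | 91.5% | 35.9% |

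At 80 per arm, formulas B and D give about 87% for .67/.87, so the choice of formula does not restore 90%.

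**The case against.** Four points can be made for the plan.

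1. *The trial may reach 90% power for the rates entered.* This stands in part. If 192 patients complete, as the Abstract and Results expect, .67/.87 has about 91.5% power. A reader might infer that the trial lacks its stated power whatever happens. The documents do not support that: for .67/.87 the shortfall applies at the planned 80 per arm, or after 20% loss from 192. It does not make 79.02 right for that pair.

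2. *The 80% may be a slip in the prose.* This is plausible. The entered pair and the 70/90 pair that returns 79.02 both have a 20-point gap, so the 10-point gain is the odd one out. The 31% figure is therefore one reading of the paragraph, not the established state of the trial. But nothing in the article says which reading is meant, and the 80% stands as the declared hypothesis.

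3. *Power for two proportions says little about the listed outcomes.* This stands. Primary Outcome Measures lists visual acuity, perimetry, OCTA and CDFI measures, and Statistical Analysis applies the t test to measurement data. No effective rate is listed. It is tempting to conclude that a null result is likely even if press needles work as assumed. That would need both 70/80 to be the real hypothesis and the effective rate to be the endpoint analysed; the documents establish neither.

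4. *The equation is missing only from the extracted text.* This stands. The paragraph announces a formula, and its absence here is no fault of the plan. The finding does not need it, since none of the standard forms gives 79.02 from a stated pair.

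**Conclusion.** The paragraph is wrong as written. It holds two irreconcilable pairs of rates, and 79.02 per arm reproduces from neither under the standard formulas with the stated deviates. The entered rates call for about 88 to 93 per arm and the hypothesised rates for about 389 to 394.

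At the planned 80 evaluable per arm, the stated 90% power is missed under both pairs: modestly for .67/.87 (about 86%), severely for 70/80 (about 31%). If all 192 are evaluable, .67/.87 passes 90% and 70/80 stays near 36%.

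These figures rest on a two-sided 0.05 test of two proportions with equal arms and the normal approximation, and they apply to an effective-rate endpoint only. The inconsistency itself rests on no assumption, since both pairs are printed. It should be corrected because the trial's size has no other stated basis.

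**What to change.** Rewrite the Sample Size Calculation paragraph with one pair of rates and an n that reproduces from them, and give power by number evaluable.

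- If .67/.87 is meant: state that about 91 per arm are needed (formula A), that 80 give about 86%, and that 96 completers give about 91.5%.
- If 70/80 is meant: drop the 90% claim and state power of about 30% to 36% for 77 to 96 per arm.
- If 70/90 was used: say so and justify the 20-point gain.

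In each case, state that the figures apply to an effective-rate endpoint that is not among the listed primary outcomes.

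The cost is the rewording of one paragraph and, depending on which pair is confirmed, a less favourable stated power. No extra enrolment is requested, and neither trial conduct nor the planned analyses change.

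### Adding 20% of 160 to reach 192 does not cover a 20% dropout: 192 leaves about 154 evaluable, and keeping 160 takes 200 enrolled

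*Protocol article*

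**What the plan says.** Under Sample Size Calculation, the protocol article sets its error rates as "α=.05 and β=0.10 in a 2-sided test", enters .67 and .87 as the two proportions, and reports the result: "This resulted in n^1^=n^2^=79.02, that is, approximately 80 cases each in the experimental and the control group", "or 160 cases in both groups". The dropout step follows. It opens with "To account for a 20% dropout rate" and ends with "the calculation 160 + (160 × 20%) = 192 suggested that 192 patients be recruited".

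Three other places bear on the point:

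- **Randomization and Allocation** builds the list on the same total, numbered 001 to 192 with 64 numbers per disease stage. Patients are "assigned randomly to either an experimental group or a control group in a 1:1 ratio".
- **Statistical Analysis** carries the last value forward for missing data, keeps such participants out of the per protocol set, and looks for consistent significance in the full analysis set and the per protocol set.
- **Results**, in the abstract and in the main text, reports 220 recruited by October 2024, of whom 192 (87.3%) are expected to complete.

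**The concern.** The 20% is applied to the wrong base. The section first fixes how many patients must remain (160) and then asks how many to recruit so that 20% can be lost. The loss is taken from the recruited number, so the required number must be divided by 0.80. Adding 20% of the required number gives a smaller total, which misses the section's own target under its own dropout assumption.

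What is at stake is the count left for analysis, mainly in the per protocol set, since dropouts are excluded from it. A reader of the section would believe that 192 protects 160 evaluable patients against a 20% loss. It does not.

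**Working it through.** **Inputs, all from Sample Size Calculation unless noted**

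- Required before dropout: 80 per group, 160 in total
- Dropout: 20%
- Two-sided α = .05 (u = 1.96), β = 0.10
- Proportions in the formula: .67 and .87
- Allocation 1:1 (Randomization and Allocation)

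**1. Reproduce the plan's figure.** 160 × (1 + 0.20) = 192. This matches exactly, and the article prints the form it used.

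**2. Number needed to keep 160.** 160 / (1 − 0.20) = 200, or 100 per group. That is 8 more than 192.

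**3. What 192 delivers at 20% dropout.** 192 × 0.80 = 153.6, about 154 in total. Per group, 96 × 0.80 = 76.8, about 77. The shortfall against 160 is about 6 patients.

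**4. Dropout that 192 does cover.** 1 − 160/192 = 0.1667, or 16.7%.

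**5. Cost in power.** Assumption: a two-sided comparison of two proportions by the normal approximation, with pooled variance under the null. With p̄ = (.67 + .87)/2 = .77,

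z = [0.20·√n − 1.96·√(2 × .77 × .23)] / √(.67 × .33 + .87 × .13) = (0.20·√n − 1.1665) / 0.5781

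| Evaluable per group | z | Power |
|---|---|---|
| 80 | 1.077 | 85.9% |
| 77 | 1.018 | 84.6% |
| 76.8 | 1.014 | 84.5% |

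The dropout step alone costs 85.9 − 84.5 = 1.4 percentage points.

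**6. Same check at the narrative rates.** The text also gives 70% for basic treatment and says "We hypothesized an 80% effective rate" for the combination. At 70% and 80%, power is 30.8% with 80 per group and 29.7% with 76.8, a loss of about 1 point. So the cost of the dropout step is similar under either pair of rates, although the power itself is very different.

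**7. Against reported recruitment.** 192/220 = 87.3% completing, so 28/220 = 12.7% lost, which is under 16.7%. The 192 completers exceed 160 by 32. Even a 20% loss from 220 leaves 220 × 0.80 = 176.

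**The case against.** The strongest reply is that events have overtaken the slip. On the figures in Results, completers exceed 160 comfortably and the loss is smaller than 192 was able to absorb. This stands as far as those figures can be relied on, and it removes most of the practical consequence. They are not fully consistent, however. The main Results text says that recruitment ran to March 2024 and also that it is expected to continue until September 2025, and the randomization list stops at 192. Nor does later recruitment make the planning sentence correct.

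A second reply is that carrying values forward keeps dropouts in the full analysis set, so the shortfall would touch only the per protocol set. That is a fair qualification, although the article's wording on how such participants are treated in the full analysis set is unclear. It does not rescue the per protocol set, in which the plan also looks for significance.

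A third reply is that the base of 160 is itself unsound. At .67 and .87 with two-sided α = .05 and 90% power, the usual formulas without continuity correction give about 88 to 93 per group, not 79.02, and the narrative rates conflict with the formula rates. This is true and a larger matter, but separate. Whatever base replaces 160, the dropout step must divide and not multiply.

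Two stronger readings are tempting. A reader might infer that the dropout step is why the trial misses 90% power. It is not: power is already 85.9% at the full 80 per group. A reader might also infer that more patients must be enrolled. The reported recruitment does not support that.

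**Conclusion.** The dropout allowance is wrong as written. Under the plan's own 20% assumption, 192 enrolled gives about 154 evaluable (77 per arm), 6 short of the stated 160. Keeping 160 would take 200, and 192 is enough only up to 16.7% dropout.

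The size is minor: about 1.4 points of power at .67 and .87. That figure rests on the normal-approximation formula above and on the effective rate used for sizing. The head counts rest only on reading the dropout rate as a share of those enrolled, which is its ordinary meaning. If the 220 recruited and 192 completers are accurate, little practical harm remains and what is left is a statement to correct.

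**What to change.** Replace the dropout sentence with one of two statements:

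- 192 enrolled allows for a dropout rate of 16.7% while keeping 160 evaluable; or
- with 20% dropout, 192 enrolled leaves about 154 evaluable (77 per arm).

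With either, give the power at that evaluable size, calculated at the effective rates once the 70%/80% in the narrative and the .67/.87 in the formula have been reconciled. If the base of 160 changes in that work, redo the dropout step by dividing by 0.80.

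The cost is one sentence and a slightly less favourable stated figure. No extra enrolment is needed, and neither the randomization nor the analysis has to change for this point.

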#### Quality Control

To guarantee the quality of the proposed experiment, a unified and standardized training program will be conducted for the researchers in each role prior to commencement of the study. Subsequently, the researchers will be subjected to a proficiency assessment, and only those deemed competent will be permitted to participate in the study. Furthermore, to enhance participant compliance, regular health education activities will be conducted, humane care will be enhanced, and a long-term follow-up plan will be developed. Finally, in accordance with the requirements set forth in the Specifications for Quality Control and Quality Assurance of Clinical Research in Chinese Medicine [19], a 4-level quality monitoring system will be established to monitor the clinically collected data on a regular monthly basis, thereby ensuring the authenticity and reliability of the study results.

### Statistical Analysis

Statistical analysis will be conducted independently by statisticians. The data will be presented as means (SDs). IBM SPSS 22.0 statistical software will be used. All statistical tests will be 2-sided tests, and the limit for statistical significance will be set at *P*<.05. The chi-square test will be performed for categorical variables, the independent Student *t* test will be used for measurement data, and the rank-sum test will be used for grade data. To evaluate the covariate balance, baseline characteristics will be summarized and compared between the experimental group and the control group using simple descriptive statistics.

Due to the expected low number of missing data, we will deal with missing data by transferring the last data item to the final dataset. This participant's data will be invalidated in the full analysis set (FAS), and this case will not be included in the per protocol set (PPS). Finally, the statistical significance of the FAS and PPS will be analyzed. A consistent statistical significance will indicate a significant difference.

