### Outcome Measures

#### Primary Outcome Measures

The primary outcomes will enable us to evaluate improvements in visual function, retinal blood circulation, and retrobulbar blood vessel circulation due to press-needle therapy. The outcomes will be as follows:

The mean change in the BCVA will be measured at baseline and 4 weeks thereafter.The mean change in the values of the pattern standard deviation (PSD), mean defect, and square root of loss variance (sLV) will be determined using an Octopus 900 perimeter at baseline and 4 weeks thereafter.The whole-image vessel density (wiVD), radial peripapillary capillary vessel density (RPCVD), superficial macula vascular density (smVD), parafoveal vessel density (paraVD), perifoveal vessel density (periVD), macular ganglion cell complex (mGCC), and peripapillary retinal nerve fiber layer (pRNFL) will be determined using optical coherence tomography angiography (OCTA) at baseline and 4 weeks thereafter.The ophthalmic artery (OA), central retinal artery (CRA), short posterior ciliary artery (SPCA), peak systolic velocity (PSV), end diastolic velocity (EDV), and resistance index (RI) will be determined using CDFI at baseline and 4 weeks thereafter.

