#### Secondary Outcome Measures

The following secondary outcomes will help us determine whether press-needle therapy improves TCM clinical symptoms and changes in the IOP:

The mean change in the IOP in the study eye will be determined uisng a TX-20P full autotonometer at baseline and at 1, 2, 3, and 4 weeks thereafter.Changes in TCM symptoms will be assessed by the investigators trained in SOPs according to the TCM Symptom Score Scale (Table S1 in Multimedia Appendix 1) at baseline and at 1, 2, 3, and 4 weeks thereafter.

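### Continuous outcomes are to be compared by an unadjusted t test, although randomisation is stratified by stage and every efficacy outcome has a baseline value: precision is lost, validity is not.

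*Protocol article*

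**What the plan says.** Randomization and Allocation states that "All eligible patients will be stratified according to early, moderate, and advanced stages of glaucoma", with stage set by cut-offs on visual field mean deviation. Each stage has its own run of 64 numbers (for the first, "The early stage will incorporate random numbers from 001 to 064"), and after stratification "the participants will be assigned randomly to either an experimental group or a control group in a 1:1 ratio". Blocking within stage is not mentioned.

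Primary Outcome Measures takes every primary outcome at baseline and week 4. Visual acuity is framed as a change ("The mean change in the BCVA will be measured at baseline and 4 weeks thereafter"), and so are the perimetry indices. The OCTA measures are only "determined using optical coherence tomography angiography (OCTA) at baseline and 4 weeks thereafter", and the colour Doppler measures are worded in the same way. In Secondary Outcome Measures, IOP is again a change ("The mean change in the IOP in the study eye will be determined"), as are TCM symptoms; both are taken at baseline and weekly to week 4.

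Statistical Analysis names three tests: chi-square for categorical variables, rank-sum for grade data and, for continuous data, "the independent Student *t* test will be used for measurement data". Baseline data have one stated use: "baseline characteristics will be summarized and compared between the experimental group and the control group using simple descriptive statistics". No adjusted model appears anywhere in the article.

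**The concern.** The design collects two kinds of information that the stated analysis leaves largely unused. A patient's baseline value usually predicts the week-4 value. Stage was thought important enough to stratify on. A two-sample t test has no place for either, except in so far as a change score subtracts the baseline.

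This is not a detail left to a later analysis plan. The article names the test, and the test does not follow from the randomisation that the article describes. What is at stake is the width of the confidence intervals, and hence the power to detect a real effect, in a trial that already holds the variables needed to do better. Naming the covariates in advance would also remove the temptation to choose them after looking at the baseline balance table.

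**Working it through.** **The plan's own figure.** There is none to reproduce on this point. The Sample Size Calculation section works with effective rates and gives no SD, no baseline to follow-up correlation and no share of variance due to stage. The correlation r and the share R² below are therefore assumptions, shown over a range.

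**Step 1: baseline.** Let the outcome have SD s at both visits and correlation r between baseline X and week 4 Y. The comparison between arms uses Y − bX, whose variance is s²(1 − 2br + b²).

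- Week-4 value alone, b = 0: s².
- Change score, b = 1: 2(1 − r)s².
- ANCOVA, b = r: (1 − r²)s².

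The ratio of ANCOVA to change score is (1 − r²)/[2(1 − r)] = (1 + r)/2. The ratio of ANCOVA to week-4 value is 1 − r². Sample size cancels from both.

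| Assumed r | ANCOVA / change-score variance | CI width ratio | Equivalent extra patients | ANCOVA / week-4-value variance | CI width ratio |
|---|---|---|---|---|---|
| 0.5 | 0.75 | 0.87 | 1/0.75 − 1 = 33% | 0.75 | 0.87 |
| 0.7 | 0.85 | 0.92 | 1/0.85 − 1 = 18% | 0.51 | 0.71 |
| 0.9 | 0.95 | 0.97 | 1/0.95 − 1 = 5% | 0.19 | 0.44 |

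CI width ratios are the square roots of the variance ratios. The change-score columns apply to visual acuity, perimetry and IOP as the article defines them. The last two columns apply to OCTA and Doppler only if their week-4 values are compared directly, which the wording leaves possible.

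**Step 2: stage.** Suppose the arms are split evenly within each stage, and stage explains a share R² of the variance of whatever is analysed (a change or a week-4 value). The true variance of the arm difference then contains only the within-stage part, 1 − R², while the t test estimates its error from the total. Its standard error is too large by about 1/√(1 − R²); for R² = 0.3 this is 1/√0.7 = 1.20. A simulation of 20,000 trials, each with three stages of 64 split 32:32, agrees:

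| Assumed R² | t-test SE / true SE | Type I error, t test | Type I error, stage-adjusted | Power, t test | Power, stage-adjusted |
|---|---|---|---|---|---|
| 0 | 1.01 | 0.046 | 0.047 | 0.896 | 0.896 |
| 0.1 | 1.05 | 0.038 | 0.050 | 0.908 | 0.925 |
| 0.2 | 1.11 | 0.030 | 0.051 | 0.918 | 0.950 |
| 0.3 | 1.19 | 0.019 | 0.053 | 0.934 | 0.972 |

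Power is for a difference of 0.468 SD, which gives 90% nominally at 96 per arm. In every row the t test's type I error is below 0.05.

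**Step 3: cost in degrees of freedom.** With 192 patients the t test has 190. ANCOVA with arm, baseline and two stage indicators has 192 − 5 = 187.

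**The case against.** The best defence is that the t test does not ignore baseline. Visual acuity, perimetry, IOP and TCM symptoms are defined as changes, so a t test on them has already subtracted the baseline value. This stands. At r = 0.9 what remains to be gained is 5% in variance, about 3% in interval width. Only OCTA and Doppler lack the word change, and the opening of the primary outcome section speaks of improvement for all outcomes, so change may be meant there too.

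A reader might infer that the t test misstates its standard error and is therefore invalid. The documents do not support that. The error in Step 2 needs arms balanced within stage, which 64 numbers per stage at 1:1 suggest but which is not stated; under simple randomisation within stage only precision is lost. It also needs stage to predict the quantity analysed. Stage should be related to the level of visual field measures, being defined from mean deviation, but stable differences between stages cancel in a four-week change, and nothing in the article says that stage predicts change. Where the error exists, it is upward and the test is conservative.

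A reader might also infer that chance baseline imbalance biases the result. Over the randomisation, t tests on change and on week-4 values are both unbiased. The imperfect correction in one particular sample is part of the efficiency loss.

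Finally, a reader might infer that weekly IOP will be tested by four separate t tests. The article does not say how the weekly values are to be combined, and that may sit in a fuller document. Nor is there ground for prescribing a stage-stratified test for categorical efficacy: the outcome sections define no such outcome, and an effective rate appears only in the sample size section.

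**Conclusion.** The point holds as one of efficiency. The article states an unadjusted test where its own design supports a more precise one at almost no cost. Against a change-score analysis the variance saving is 25%, 15% or 5% at r = 0.5, 0.7 or 0.9. Against a direct comparison of week-4 values, possible for OCTA and Doppler, it is 25%, 49% or 81%. These figures rest on equal SDs at the two visits and on assumed correlations.

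The further effect of leaving out stage is conditional on balance within stage and on stage predicting the analysed quantity. It makes the test conservative and may be small for four-week changes. The plan as written would not produce biased estimates or excess false positives from this source.

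**What to change.** In Statistical Analysis, replace the t test for each continuous efficacy outcome with ANCOVA of the week-4 value on arm, baseline value and stage stratum, and report the adjusted difference between arms with its 95% CI. Use the same form for OCTA and Doppler, which also settles whether changes or week-4 values are compared. For perimetry, baseline value and stage overlap because stage is cut from mean deviation; keeping both terms is harmless and follows the randomisation.

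For weekly IOP, one mixed model for repeated measures with arm, week, arm by week, baseline and stage, and week 4 as the named contrast, is a reasonable option.

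Specify this before database lock, while the statisticians are still blinded as the Discussion states. No new measurement is needed, since baseline values and stage are scheduled for every participant. The cost is three degrees of freedom, revised analysis wording, and the submission that Ethical Considerations requires when analyses change.
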